#### More outcomes up to term equivalent age

- Mortality (binary outcome)
- White matter disease (periventricular leucomalacia, binary)
- Septicaemia (binary)

Brain abnormality scores from [Kidokoro et al. \(2013\)](#) will be used instead of the brain maturation scores described by [Leuchter et al. \(2014\)](#).

This outcome will be assessed for all recruited children in only one center, as opposed to the other cUS outcomes that were assessed in each center. An amendment of the study protocol is planned for this new secondary outcome.

These secondary outcomes are mentioned in the study protocol from Zürich, Version 1.11 from March 20, 2017, but not in the protocol paper by [[name] et al. \(2015\)](#)

- Necrotising enterocolitis or focal gastrointestinal perforation (FIP) (binary)
- Bronchopulmonary dysplasia (oxygen dependency at 36 weeks PMA, binary)
- Retinopathy (binary)
- Length of stay in hospital (days)

#### 2.2.4 Other outcomes

The outcomes listed here (measured at 28 DOL and/or 36 weeks PMA) will only be analyzed descriptively:

- Severity of anaemia
  - Hematocrit (%)
  - Hemoglobin (g/dl)
  - Number of transfusions
- Weight (g)
- Head circumference (cm)
- Length of supplemental O2 (PMA at last day with supplemental O2)
- Total number of days with supplemental O2

### 3 Hypothesis

The alternative hypothesis for the primary endpoint is that EPO improves the intelligence quotient at 5 years of age compared to Placebo. The null hypothesis is no improvement with regard to the primary endpoint by EPO compared to Placebo.

Although the main study hypothesis is one-sided, we will apply two-sided tests. Estimates and confidence intervals will provide information about the direction of potential differences between the EPO and the Placebo arm.

### 4 Analysis data set

The **full analysis set (FAS)** will contain all children randomized to the trial whose parents gave informed consent, except one child who had to be excluded from the study after randomization due to severe genetic damage which was an exclusion criterion (another child was recruited instead).

Due to missing outcome measurements (and maybe explanatory variables) we will use multiple imputation to be able to analyze the complete FAS (see also Sections 5.1 and 8). In addition, we will do complete case analyses and optionally apply a special method to account for missing data due to death (sensitivity analysis S4 in Section 5.1).

## 5 Planned analyses

The statistical analysis will be performed in three stages, including (1) secondary outcomes measured up to term equivalent age, (2) secondary outcomes measured after 2 years follow-up and (3) the primary outcome and secondary outcomes measured after 5 years follow-up.

All statistical analyses will be performed using the Statistical software environment R ([R Core Team, 2018](#)). We will always report estimates and 95 % confidence intervals (corresponding to a significance level of 0.05) together with p-values. Information on specific R packages is given below. Due to the large number of secondary outcomes, we will adjust p-values for the comparison of secondary outcomes among treatment arms for multiplicity, using the Bonferroni-Holm method ([Holm, 1979](#)) and report them alongside the unadjusted p-values.

### 5.1 Primary analysis

The primary outcome, IQ measured by Kaufman-ABC (or SON-R), will be compared between treatment arms (EPO vs. Placebo) using a linear mixed-effects model with "treatment" as fixed explanatory factor and a random intercept per "center". This will result in an estimate (and 95 % CI) of the EPO treatment effect on IQ. The model assumptions will be checked by visual assessment of the residuals and log-transformation of the primary outcome may be considered in case of violations. We will use the R package lme4 ([Bates et al., 2015](#)) to fit the models and the R package lmerTest to derive p-values via the Satterthwaite approximation ([Kuznetsova et al., 2017](#)).

It has to be noted, that a comparison of IQ among survivors who performed an IQ test is prone to bias due to the large proportion of children who die before the age of 5 years and due to other losses to follow-up (20 % loss was expected in total, ca. 15 % of the newborn babies already died in hospital). The bias would be particularly high if the reasons for, or the frequency of, losses differed between trial arms (see e.g. [Altman, 2009](#)). Adhering to the method proposed in the protocol and its published version ([[name] et al., 2015](#)), we will use multiple imputation for the missing IQ values ([van Buuren and Groothuis-Oudshoorn, 2011](#)). We thereby assume that data are missing at random (MAR) and we treat missingness due to death in the same way as missingness due to other reasons. For more details see Section 8. The analysis will be performed on the FAS, in line with the intention-to-treat (ITT) principle.

The following sensitivity analyses will be done in addition to the "main primary analysis" just described:

- S1 Covariate adjusted analysis with birth weight of the child, severity of the intraventricular hemorrhage (Grade II, III or IV), steroid administration before birth, steroid administration after birth and Socio-Economic Score (SES) of the mother as additional explanatory variables compared to the main primary analysis.
- S2 Model described for the main primary analysis but performed on the complete cases in the FAS only (without multiple imputation, not in line with ITT)
- S3 Optional: model described for the main primary analysis but performing a modified version of multiple imputation, using the random indicator method ([Jolani, 2012](#)) to account for "non-ignorable missing data" (to handle the problem that children for whom IQ data are missing may differ from those with IQ data even after accounting for the observed information).
- S4 Optional: the method proposed by [Hayden et al. \(2005\)](#), which specifically deals with missing data due to death (as opposed to missing data in patients that are alive), will be applied. This

method of principal stratification will estimate a "survivor average causal effect" (SACE), a concept introduced by (Rubin, 2000). The SACE would be the effect of Epo on those children who would have survived under both treatments (Epo and Placebo).

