### 4.1 Background and Rationale

Approximately 1% of all infants are born very preterm with a birth weight (BW) <1'500 g and a gestational age (GA) below 32 completed weeks of gestation (VLBW: very low birth weight). Although more than 85% of these VLBW infants survive, roughly 40% of survivors are affected by neurodevelopmental impairment and learning disabilities upon entering school. One of the most consistent predictors of neurodevelopmental impairment is intraventricular haemorrhage (IVH), which occurs in approximately 20% of all VLBW infants, mostly within the first few days after birth. Among VLBW infants, increased prematurity at birth, higher rates of IVH and a higher likelihood of neurodevelopmental impairment are directly linearly related. Infants with large IVH (grade III or IV, the latter of which is now often also termed "haemorrhagic parenchymal infarction"), especially those requiring shunt insertion for posthaemorrhagic hydrocephalus, are the most severely affected, though infants with low-grade IVH (grade I or II) have reduced brain cortical volume and lower developmental scores. In addition to immediate parenchymal damage and free iron toxicity, IVH results in the loss of germinal matrix precursor cells and negatively affects contralateral cerebellar growth, which contributes to long-term cognitive, learning, and behavioural disability. There are very few evidence-based measures to reduce the risk of IVH, such as foetal lung maturation or late cord clamping. The incidence of IVH among VLBW infants has declined only slightly over the last two decades, in contrast to other forms of brain damage such as periventricular leukomalacia (PVL). Except for shunt insertion to divert cerebrospinal fluid in infants with posthaemorrhagic hydrocephalus and possibly the removal of blood clots in infants with high-grade IVH, there is no treatment for established IVH, and no medical therapies exist to ameliorate the neurodevelopmental sequelae of IVH.

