### **8.3 Method of Assigning Subjects to Treatment Groups**

EPO as a verum is compared to NaCl 0.9% as a placebo 1:1. Randomization lists for block randomization will be performed for each participating study cite separately by the CTC Zürich.

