#### **Hypotheses:**

The alternative hypothesis for all endpoints is improvement with regard to the endpoint in the group of EPO-treatment. The null hypothesis for all endpoints is no improvement with regard to the endpoint in the group of EPO-treatment compared to the control group.

The study hypotheses are one-sided – however, the tests will be performed 2-sided yielding corresponding confidence intervals and accordingly information about the direction of a potential difference between control and treatment group.

The significance level alpha is 0.05.

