## 12.5 Determination of Sample Size

Information about effect size and standard deviation of the primary endpoint (IQ outcome at age of 5 years) can only be derived from one observational study presented by Neubauer AP et al. who investigated the effect of EPO-treatment of VLBW infants on composite IQ at 10 years.

Neubauer AP et al. included in their study all grades of IVH, also the lowest, IVH I°. However, diagnosis of IVH I° may be missed or even overestimated in very preterm infants. Neubauer AP et al. reported on no difference in infants without IVH regarding composite IQ at 10 years between EPO-treated and untreated, hence we decided to exclude infants with borderline diagnosis of IVH I° to avoid bias from misdiagnosis.

Neubauer et al. reported for the relevant group of children who suffered IVH an effect size between EPO-treated (IQ=90.3) vs. untreated (IQ=67.0) of 23, standard deviation (SD) 21,  $p < 0.01$ . Given that the vast majority of children will remain on their 5-year IQ trajectory, and there is good agreement between classification of cognitive abilities at 5 and 11 years of age, we used this continuous outcome parameter (effect size 23) for power analysis.

To determine the required sample size for the primary outcome we performed a power calculation for a 2-sample t-test assuming a significance level of  $\alpha=0.05$ ,  $SD=21$  of the outcome, and a 1:1 randomization. As result we get as required total sample size  $n=28$  (for both groups together), and  $n=38$  for a power ( $1-\beta$ ) of 0.8 and 0.9, respectively.

When assuming a smaller effect size of 10 (instead of 23), a SD of 15 (instead of 21 because IVH I° will be excluded in our study group to avoid misdiagnosis leading to a sample which is less heterogeneous with regard to the primary outcome) and a power of 0.8, the required total sample size is  $n=72$ .

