## 9 Deviations from the original statistical plan

The statistical analyses proposed in this document are generally in line with those proposed in the protocol and its published version ([name] et al., 2015), but include a few slight modifications or additions:

- Brain abnormality scores from Kidokoro et al. (2013) will be used as secondary outcomes instead of the brain maturation scores described by Leuchter et al. (2014) (see footnote above).
- Composite cUS scores will be centrally assessed, in addition to the cUS outcomes that are assessed in each center (see footnote above).
- Some outcomes were only listed in the study protocol (Zürich, Version 1.11 of March 20, 2017) but not in the published version ([name] et al., 2015) (see footnote above).
- "Other outcomes" listed in Section 2.2.4 were not listed anywhere before and are therefore only analyzed descriptively
- Due to the large number of centers compared to the number of patients we use a random intercept per center instead of modelling center as fixed effect. This allows to include additional covariates, as specified in sensitivity analysis S1.
- The sensitivity analysis S3 was added to assess the assumption of missingness at random (MAR) and S4 was added because missingness of data due to death is different from missingness that arises when a patient still alive is not measured.

These deviations and all deviations (if any) from the statistical analysis plan outlined in this document will be listed in the statistical analysis report.

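### Adding baseline IVH grade and gestational age to the main primary model would be a cheap precision gain; at present only centre is adjusted for there

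*Combined protocol and SAP*

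**What the plan says.** **Main model.** SAP 5.1 compares IQ between arms with a linear mixed model that has treatment "as fixed explanatory factor and a random intercept per" centre. It contains no patient-level baseline variable.

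**Allocation.** Protocol 8.3: "Randomization lists for block randomization will be performed for each participating study cite separately". SAP section 1 confirms 1:1 blocks within each of nine centres. No stratification by IVH grade or gestational age is stated.

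**Prognosis.** Protocol 4.1 says that among VLBW infants "increased prematurity at birth, higher rates of IVH and a higher likelihood of neurodevelopmental impairment are directly linearly related", and it singles out grade III and IV infants as the worst affected. Protocol 12.3 names gestational age, birth weight and maternal age as covariates for its third, regression-adjusted level of inference. Gestational age, birth weight and maximal IVH extent are recorded at visit 0 (protocol 6.2).

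**Where adjustment happens.**
- Sensitivity analysis S1 adds birth weight, IVH grade (II, III or IV), steroids before birth, steroids after birth and socio-economic score (SES).
- SAP 5.2.2 applies the same set to BSID-III as a sensitivity analysis.
- SAP 5.2.1 tests a treatment interaction with infarction.
- SAP section 8 uses all relevant baseline variables for imputation.

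SAP section 9 explains the random centre intercept by the large number of centres relative to patients, and adds: "This allows to include additional covariates, as specified in sensitivity analysis S1".

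**The concern.** IVH grade and prematurity are the baseline features that the protocol itself links to impairment. With about 120 infants enrolled and about 80 expected to have an IQ, their balance between arms is left to chance. The headline estimate and p-value will not correct for any imbalance, nor use the IQ variation that these variables explain.

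S1 only partly fills the gap:
- Steroids after birth are recorded as a summary of the whole hospital stay (protocol 6.6), so they may follow the start of treatment.
- SES is scored at 2 and at 5 years (protocol 6.8 and 6.9).
- Gestational age is missing from S1; birth weight is only a partial proxy.

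S1 is therefore not a clean baseline adjustment. The SAP also does not say how to read the trial if S1 and the main analysis disagree. Finally, the move from the protocol's covariate set to the S1 set, which drops gestational age and maternal age, is not among the changes listed in section 9.

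**Working it through.** **1. Reproduce the plan's figure.** Inputs from protocol 12.5: "When assuming a smaller effect size of 10 (instead of 23), a SD of 15 (instead of 21") "and a power of 0.8, the required total sample size is" 72. Protocol 12.2 adds: "The significance level alpha is 0.05". SAP section 3 adds: "Although the main study hypothesis is one-sided, we will apply two-sided tests".

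n per arm = 2(1.960 + 0.842)² × 15² / 10² = 35.3, rounded up to 36, so 72 in total. The noncentral t gives 36.3 per arm. The figure reproduces.

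**2. Planned power without covariates.** The documents expect 80 children at visit 6, so 40 per arm.

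SE = 15 × √(4/80) = 3.354. Noncentrality = 10/3.354 = 2.98 on 78 df. Power = 0.838. The 95% CI half-width is 1.96 × 3.354 = 6.57 points.

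**3. Power with IVH grade and gestational age.** Three levels of IVH grade cost two parameters and gestational age costs one, so k = 3. Let R² be the share of IQ variance that they explain jointly. **R² is an assumption, shown as a range.** Estimating k covariate terms inflates the variance of the treatment effect on average by (N − 3)/(N − 3 − k) = 77/74 = 1.041, and the residual df are 75:

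SE = SD × √(1 − R²) × √(4/80 × 1.041)

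| SD | R² | SE | 10/SE | Power | CI half-width |
|---|---|---|---|---|---|
| 15 | unadjusted | 3.354 | 2.98 | 0.838 | 6.57 |
| 15 | 0 | 3.421 | 2.92 | 0.823 | 6.71 |
| 15 | 0.05 | 3.335 | 3.00 | 0.841 | 6.54 |
| 15 | 0.10 | 3.246 | 3.08 | 0.860 | 6.36 |
| 15 | 0.20 | 3.060 | 3.27 | 0.897 | 6.00 |
| 15 | 0.30 | 2.863 | 3.49 | 0.932 | 5.61 |
| 21 | unadjusted | 4.696 | 2.13 | 0.557 | 9.20 |
| 21 | 0.20 | 4.284 | 2.33 | 0.635 | 8.40 |

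Simulation of the regression with three IVH levels and gestational age (SD 15) agreed: power 0.823, 0.860, 0.901 and 0.933 at R² 0, 0.10, 0.20 and 0.30. Type I error was about 5% with and without covariates.

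**4. Chance imbalance.** Suppose 30% of infants have an infarction (assumed). The exact binomial chance that the arms differ by 10 percentage points or more is 0.27 with 60 per arm and 0.39 with 40 per arm. If infarctions and other infants differed by 15 to 20 IQ points (also assumed), such an imbalance would move the unadjusted difference by 0.10 × 15 = 1.5 to 0.10 × 20 = 2 points.

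More generally, the 95% range of the chance shift that adjustment removes is ±1.96 × √R² × 15 × √(4/80), which is ±2.1, ±2.9 and ±3.6 points at R² 0.10, 0.20 and 0.30. This is the same gain as in step 3 seen another way, and must not be added to it.

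**The case against.** The strongest reply is that the plan already covers most of this. S1 is mandatory (only S3 and S4 are optional), adjusts for IVH grade and birth weight, and is carried over to BSID-III. The main model matches the second level in protocol 12.3, is valid under randomisation, and has 0.84 power on the plan's own assumptions, above the 0.80 target. All of that stands, and it makes this an improvement, not the repair of an error.

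Three further points stand:
- No document gives an R². The sentence in protocol 4.1 concerns VLBW infants in general, not variance explained within grades II to IV, and it implies that prematurity and IVH overlap as predictors.
- The power figures are for complete cases, while the main analysis imputes IQ over the full analysis set with baseline variables in the imputation model. The figures therefore do not carry over exactly. But imputation uses those variables only to fill in missing scores; it does not adjust the contrast among the observed ones.
- The gain is not free: it costs three degrees of freedom.

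A reader might infer that section 9 contradicts itself by making room for covariates and then leaving them out of the main model. It does not: the reason given is the number of centres, and the covariates are assigned to S1, where they appear.

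**Conclusion.** The point holds as a cheap improvement. The main primary model leaves out two prognostic variables that are known at visit 0 and not balanced by design, and the one adjusted analysis mixes baseline with later covariates and omits gestational age. At 80 children and SD 15, adjustment would bring power from 0.84 to about 0.86–0.93 for R² of 0.10 to 0.30, and narrow the interval by 3% to 15% (6.57 to 6.36 and to 5.61 points). At SD 21, the figure that protocol 12.5 takes from the observational study, power would go from 0.56 to about 0.64 at R² 0.20. If the covariates explained nothing, power at SD 15 would slip to about 0.82.

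All of this rests on the assumed R², a complete-case approximation and no allowance for centre effects. The imbalance figures rest on an assumed infarction share and IQ gap.

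Two stronger readings are not supported. The unadjusted comparison is not biased or invalid: chance imbalance is already reflected in its standard error. Nor does the plan ignore IVH grade, which is in S1 and, as infarction, in a subgroup analysis. The omission from every named SAP analysis model concerns gestational age.

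**What to change.** Make the main primary analysis a linear mixed model with treatment, visit-0 IVH grade (II/III/IV) and gestational age at birth as fixed effects and a random intercept for centre. Keep the treatment-plus-centre model as a sensitivity analysis. In section 9, list this change and state that gestational age and maternal age, named in protocol 12.3, were left out of S1.

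The cost is SAP wording and three degrees of freedom; no new data are needed. Timing is the real constraint. SAP section 5 analyses outcomes in three stages with IQ last, and the protocol's publication policy foresees publishing MRI and ultrasound results before the primary outcome. The covariates must therefore be fixed before any results by arm are seen, that is before stage 1. A change of primary model after that would be open to the charge of a post hoc choice.

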#### **7.5.1 Data Collection and Follow-up for Withdrawn Subjects**

If data are missing, e.g. not collected, they can be included in final analysis. We believe that few missing data are acceptable and are not influencing the study results. In case of subject withdrawal all data collected until withdrawal will be saved. After completing study analysis data of withdrawn subjects will be anonymized ~~unless parents explicitly abstain from making data anonymous.~~

To optimize data quality and to minimize queries by the monitors of the CTC Zürich, the local PIs will be supported in data input by the study staff, especially by the study nurse and by the co-investigator. Both, the study nurse and the co-investigator will visit each study site at least once and will help with data input in the eCRFs especially on request in case of problems.

To increase follow up rate and minimize drop outs, parents of participating subjects will receive financial compensation if necessary for participation in the visits after discharge, visit 4 (brain MRI), visit 5 (FU2) and visit 6 (FU5). There will be no regular amends. But if parents have to take off from work to participate visit 4 to 6 and/or complain travel expenses, the sponsor will reimburse these upon request.

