Based on the only available data of Neubauer et al. and the just mentioned reduction of the assumed effect size to 10 (instead of 23) and SD to 15 (instead of 21) we set the target sample size for visit 4, the secondary endpoint 'MRI at term equivalent age', at  $n=50$  for EPO and  $n=50$  for placebo. Given a 20% loss to follow up until 5-year,  $n=80$  will meet the primary endpoint, visit 6. This number is in line with the result of the power analysis presented above. Hence, to achieve the target sample size for visit 4 of  $n=100$  and an assumed early loss by about 15% due to e.g. death in this high-risk VLBW infant population,  $n=120$  VLBW infants with IVH II-IV have to be enrolled in this trial.

According to data of the Bundesamt für Statistik ([www.bfs.admin.ch](http://www.bfs.admin.ch)) and the Swiss neonatology register (Minimal Neonatal Dataset, MNDS, [www.neonet.ch](http://www.neonet.ch)) more than 800 very low birth weight (VLBW) infants were born each year since 2007 in Switzerland. The participating 8 Swiss neonatology level III units treat more than 80% of all VLBW infants in Switzerland ( $n>700$  per year). To increase the number of eligible VLBW infants per year, the neonatology units of the University hospitals in Berlin (Charité) and Wien will contribute, treating together about 400 VLBW infants per year. Together, at all 9 study sites, more than 1000 VLBW infants will be assessed for eligibility each year.

As this trial offers a unique chance to receive a potentially beneficial treatment for IVH, the majority of parents are expected to be sympathetic to the trial (70%). Together, to achieve a target sample size of n=80 for the primary endpoint (visit 6) a total number of 1670 VLBW infants have to be assessed for eligibility:

- assessed for eligibility n=1'6700 VLBW infants → 12% have IVH grade 2-4
- presence of IVH II-IV n=200 VLBW infants (IVH II-IV) → 15% loss due to exclusion criteria
- asked for participation n=170 VLBW infants (IVH II-IV) → 30% no parental consent
- to be enrolled in trial n=120 VLBW infants (IVH II-IV) → 15% early loss (death)
- to be analyzed at visit 4 n=100 VLBW infants (IVH II-IV) → 20% loss at 5-year follow-up
- to be analyzed at primary endpoint (visit 6) n=80 VLBW infants (IVH II-IV)

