## 8 Handling of missing data and drop-outs

We will multiply impute missing outcome and covariate data due to death or loss to follow-up in the FAS. Multiple imputation will be performed by the R package mice ([van Buuren and Groothuis-Oudshoorn, 2011](#)), and will be applied separately at each stage of analysis (see Section 5). The imputation model will use all relevant baseline variables, the randomized treatment and outcome variables collected up to the time of analysis, potentially using correlations among outcomes for imputation in case the amount of missing data differs among outcomes. We will produce  $m=20$  imputations per missing value and analyze the 20 resulting complete data sets using Rubin's rules to pool the results.

While multiple imputation assumes missingness at random (MAR), missingness not at random can be investigated using the random indicator method proposed by [Jolani \(2012\)](#), mentioned also in [van Buuren \(2018\)](#). The latter will be used for sensitivity analysis S3.

In addition, a principal stratification approach suggested by [Hayden et al. \(2005\)](#) may be applied in order to estimate the "survivor average causal effect" (SACE), as proposed for sensitivity analysis S4.

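### SAP 5.1 gives 20% as the total expected loss where protocol 12.5 plans about a third, and with 20 imputations a borderline primary p-value depends noticeably on the random draw

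*Combined protocol and SAP*

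**What the plan says.** **Planned loss.** Protocol 12.5 enrols 120 infants, takes off about 15% early loss (mainly death) to reach 100 at visit 4, then takes 20% off those 100 by 5 years. The chain ends with "to be analyzed at primary endpoint (visit 6) n=80 VLBW infants (IVH II-IV". The synopsis repeats 120, 100 and 80. SAP 5.1, in a parenthesis within its warning about bias, says "20 % loss was expected in total, ca. 15 % of the newborn babies already died in hospital".

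**What is imputed.** SAP 4 and 5.1 analyse the full analysis set and impute every missing IQ under MAR, treating deaths and other losses alike. SAP 8 plans 20 "imputations per missing value and analyze the 20 resulting complete data sets", pooled by Rubin's rules. The imputation model draws on relevant baseline variables, treatment and outcomes collected up to the time of analysis. No reason is given for 20, and no seed or Monte Carlo error target is stated.

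**Test.** Protocol 12.2: "The significance level alpha is 0.05" and "the tests will be performed 2-sided yielding corresponding confidence intervals".

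**The concern.** The two loss figures cannot both describe the same trial. A total of 20% leaves 96 of 120 children with an IQ; the protocol plans for 80. The SAP figure looks like the protocol's second-stage rate (100 to 80) taken for the whole. Because deaths are imputed too, total loss is the share of the primary outcome that is imputed, so a reader of the SAP alone would underestimate that share.

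That share also bears on the number of imputations. The more information is missing, the more a pooled result varies between runs at a fixed m. If the primary p-value comes out near 0.05, two analysts following the same SAP with different seeds could report results on opposite sides of the threshold.

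**Working it through.** **1. The protocol's own figure.** Protocol 12.5: "When assuming a smaller effect size of 10 (instead of 23), a SD of 15" "and a power of 0.8, the required total sample size is" 72. Check, per arm: 2 × (1.960 + 0.842)² × 15² / 10² = 35.3, rounded up to 36, so 72 in total. The exact t calculation gives 74. The figure reproduces.

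**2. The attrition chain.**
- By headcount: 1 − 80/120 = 33.3%, or 40 missing.
- By chained rates: 1 − 0.85 × 0.80 = 32.0%; 120 × 0.32 = 38.4 missing.
- SAP 5.1: 120 × 0.20 = 24 missing, 96 measured.
- If 15% die and total loss is 20%, later loss among survivors is 1 − 0.80/0.85 = 5.9%, against the protocol's 20%.
- Protocol 4.6 cites follow-up rates of 87% and 78%. With 15% early loss these give totals of 1 − 0.85 × 0.87 = 26% and 1 − 0.85 × 0.78 = 34%.

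**3. Power.** With 40 per arm, expected z = 10 / (15 × √(2/40)) = 2.98, giving power of about 0.84 and p of about 0.004 at the expected result. The sample size already uses the 120-to-80 chain, so the SAP wording does not touch it.

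**4. Monte Carlo error, analytic.** The SD of the pooled estimate between imputation runs, in standard-error units, is √(FMI/(m + 1)), where FMI is the fraction of missing information. The documents do not give FMI, so it is assumed. At FMI 0.33 and m = 20 this is √(0.33/21) = 0.125. Around z = 1.96, ±1.96 × 0.125 moves p = 0.05 to about 0.027 to 0.087. This is a lower bound on the spread, because the estimated standard error varies between runs as well.

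**5. Monte Carlo error, simulated.** The setup was 60 children per arm, SD 15, with 40 or 24 IQs missing, Bayesian linear-regression imputation and Rubin's rules with small-sample degrees of freedom. One data set with a long-run p of 0.05 was re-imputed 2,000 times (500 times for m = 200). Central 95% range of p between runs:

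| Missing | FMI (assumed auxiliary correlation) | m = 20 | m = 100 | m = 200 |
|---|---|---|---|---|
| 40 | 0.35 (none) | 0.022–0.103 | 0.034–0.069 | 0.039–0.064 |
| 40 | 0.27 (0.5) | 0.025–0.092 | 0.037–0.066 | 0.041–0.062 |
| 40 | 0.20 (0.7) | 0.029–0.083 | 0.039–0.062 | 0.043–0.059 |
| 24 | 0.21 (none) | 0.029–0.086 | 0.039–0.064 | 0.042–0.059 |
| 24 | 0.10 (0.7) | 0.035–0.070 | 0.043–0.058 | 0.044–0.055 |

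**6. When the decision is at risk.** With 40 missing, no auxiliary information and m = 20, a long-run p of 0.03 lands above 0.05 in 13% of runs, and one of 0.08 lands below it in 11%. With auxiliary correlation 0.7 these fall to 4% and 3%. At FMI 0.33, a long-run p of 0.01 stays below 0.05 in 99.8% of runs, and one of about 0.004 stays below in all of them.

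**The case against.** **The 20% drives nothing.** This stands. It is a remark in parentheses. No sample size, model or choice of m is derived from it, and the protocol carries the right chain. It is a wording error about how much will be imputed.

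**The instability is conditional.** This also stands. A reader might infer that m = 20 makes the primary p-value unreliable in general. The calculations do not support that: the significance decision is exposed only for a long-run p of roughly 0.02 to 0.10. Such a result is not remote, though. Taking z as normal around 2.98 with SD 1, the chance of p between 0.02 and 0.10 is Φ(2.33 − 2.98) − Φ(1.64 − 2.98), about 17%, even if the design effect is true.

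**The SAP will use auxiliary variables.** True, and good predictors narrow the range, as the table shows. The gain is partial, since children who die in hospital have no 2-year data. At an assumed correlation of 0.7 the m = 20 range is still 0.029 to 0.083.

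**More imputations do not remove seed dependence.** Correct. At m = 200 a p-value centred on 0.05 still straddles it. Raising m shrinks the spread, a seed makes the number repeatable, and reported Monte Carlo error shows what spread remains.

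**Two further inferences the documents do not support.** A reader might infer that the 20% plays down the MAR assumption. SAP 5.1 warns in the same paragraph of bias from the large proportion of deaths, states MAR openly, and adds a complete-case analysis (S2) with optional analyses for non-ignorable missingness (S3) and survivor effects (S4). A reader might also want to strike the sentence in protocol 7.5.1, "We believe that few missing data are acceptable and are not influencing the study results". It concerns uncollected items and withdrawn subjects and does not describe the expected 5-year loss as few. Protocol 12.4 and SAP 8 govern missing outcomes, so deleting it would change no analysis.

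**Conclusion.** The SAP's total is wrong as written: the protocol plans a loss of 32% to 33%, so about 38 to 40 of 120 primary outcomes would be imputed, against 24 implied by the SAP. This rests on the documents alone.

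The point about m holds in a limited form. At m = 20 a primary p-value near 0.05 varies between runs over about 0.02 to 0.10 at a missing-information fraction of about one third, and about 0.03 to 0.08 at 0.20. Both fractions are assumptions. The simulation used a two-group linear analysis without the random centre intercept, so the ranges are indicative. At the result expected under the design assumptions the conclusion is unaffected. More imputations do not settle whether IQ after death can be treated as missing at random. The change is worth making because it is nearly free and can be settled before the 5-year analysis.

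**What to change.** **SAP 5.1.** Replace the first clause of the parenthesis with: *about one third loss was expected in total (120 enrolled to 80 at 5 years: about 15% early loss, then 20% of those remaining)*. Keep the in-hospital death figure that follows. The wording says *about one third* because the chained rates give 38.4 of 120 and the headcounts give 40.

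**SAP 8.** Raise m to at least 100. A value of 200 is better and costs only computing time; it is a preference over 100, not a threshold. Pre-state the random seed. Report the Monte Carlo error of the primary estimate and p-value.

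**Cost.** A few SAP edits and some computing time. No protocol text needs to change.
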